### Exploratory Endpoints

For each exploratory evaluation variable, descriptive statistics will be presented at baseline, 12 weeks, and 24 weeks. The change from baseline to 12 weeks or 24 weeks will be analyzed using a Paired t-test or Wilcoxon signed rank test.

1. **Safety Endpoints**

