4. Collect physical measurements (height) and body composition analysis information. Height is collected only at Visit 1 (Baseline, Day 0) to the first decimal place. Body composition analysis (skeletal muscle mass, body fat mass, body fat percentage, waist/hip circumference, etc.) is collected at each visit using InBody770.
5. After at least 5 minutes of rest, collect vital signs (systolic blood pressure, diastolic blood pressure, pulse rate). If there are measurement results at each visit, collect these results.
6. Collect information on Type 2 diabetes (date of diagnosis).
7. For medical history, collect past medical history within 6 months prior to Visit 1 (Baseline, Day 0) and current medical conditions at the time of enrollment.
8. Laboratory tests are collected if conducted as part of routine clinical practice. If there are HbA1c results within 4 weeks prior to Visit 1 (Baseline, Day 0) or other test results within 3 months prior to Visit 1, these results can be used in place of the laboratory tests at Visit 1 (Baseline, Day 0). Examples of laboratory test items are as follows.

| Main Laboratory Tests | HbA1c, FPG, Creatinine, eGFR, TC (Total Cholesterol), HDL, LDL, TG (Triglyceride), UACR, UGCR |
| --- | --- |
| Other Laboratory Tests  (Blood Tests) | RBC, Hemoglobin, Hematocrit, Platelet, WBC, Differential WBC count (Basophil, Eosinophil, Neutrophil, Lymphocyte, Monocyte), Na, K, Cl, P, Ca, Mg, BUN, LDH, Uric Acid, ALT, AST, ALP, γ-GTP, CPK, Total Bilirubin, Albumin, Total Protein, Glucose^*^, Insulin^*^ |
| Other Laboratory Tests  (Urinalysis) | pH, Specific Gravity, Bilirubin, Ketone, Nitrite, Protein (Albumin), RBC (Occult Blood), Urobilinogen, WBC (Leukocyte), Glucose, Creatinine |

*According to the calculation formulas, HOMA-beta is calculated as [360×fasting insulin concentration (μU/mL)×fasting glucose (mg/dL)-63], and HOMA-IR is calculated as [fasting insulin concentration (μU/mL)×fasting glucose (mg/dL)/405].

1. - Prior medications: Collect information on diabetes medications used specifically for the treatment of Type 2 Diabetes within 4 weeks prior to Visit 1 (Baseline, Day 0). This includes the drug name (generic or brand name), duration of administration (start date, end date, ongoing status), single dose amount/unit, daily administration frequency, and route of administration.

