## Rationale

This study is a large-scale, prospective, multicenter, non-interventional database observational study aimed at observing the weight loss effects, efficacy, and safety of Envlo Tab./Envlomet SR Tab. in patients with Type 2 diabetes over 24 weeks.

As a single-arm observational study, the number of subjects was calculated using G*Power 3.1.9.7, referencing the mean and standard deviation of the changes in weight and body mass index (BMI) from baseline to 12 or 24 weeks from previous Phase 2 and Phase 3 clinical studies (Figure 2) ^20)^

[Assumptions]

- Effect size: 0.25 (Mean of difference 2.5, SD of difference 10.0)
- Power: 0.95
- α error: 0.05
- Drop-out rate: 30%

[figure not shown]

Figure 2. Sample Size Calculation (G*Power)

Based on previous studies, assuming an average weight change of 2.5 kg and a standard deviation of 10.0 for the intervention with Envlo Tab. or Envlomet SR Tab., the effect size is 0.25. Setting the power: 0.95, α error: 0.05, the total required sample size is estimated to be approximately 210 subjects. Considering a drop-out rate of about 15%, we plan to recruit around 240 subjects.

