## Procedure and Schedule of Observational Study

### Visit Schedule

There are no mandatory visits, tests, laboratory tests, or treatments in this study. Data will be prospectively collected using medical records, investigator assessments, and laboratory test results from routine clinical visits. Each investigator will collect predefined information from subjects at baseline and during the follow-up period.

1. **Visit 1 (Baseline, Day 0)**

At the first visit (baseline), the following information will be collected:

- Obtain subject consent and assign subject enrollment number
- Inclusion/Exclusion Criteria Confirmation
- Demographic information [initials, gender, age (month and year of birth), pregnancy and breastfeeding status]
- Alcohol/Smoking/Lifestyle information
- Physical measurements (height, weight)
- Body composition analysis (include BMI, skeletal muscle mass, body fat mass, body fat percentage, etc.)
- Vital signs (systolic/diastolic blood pressure, pulse rate)
- Information on Type 2 Diabetes (Diagnosis date)
- Medical history (Past medical history within 6 months prior to enrollment (excluding the target disease) and current medical history)
- Prior medications (diabetes treatments within 4 weeks prior to enrollment) and concomitant medications (all medications, including diabetes treatments, taken at the time of enrollment).
- Laboratory tests (HbA1c, FPG, Total Cholesterol, LDL-C, HDL-C, Triglyceride, ALT, AST, Creatinine, e GFR, UACR, UGCR, etc.)
- Administration Information of Envlo Tab. or Envlomet SR Tab.

1. **Follow-Up Visits**

Follow-up visits will be conducted at 12-week intervals from the first visit (baseline) as Visit 2 (12 weeks ±2 weeks) and Visit 3 (24 weeks ±2 weeks). During follow-up visits, the following information will be collected:

- Alcohol/Smoking/Lifestyle information
- Physical measurement (weight)
- Vital signs (systolic/diastolic blood pressure, pulse rate)
- Body composition analysis (include BMI, skeletal muscle mass, body fat mass, body fat percentage, etc.)
- Concomitant medications
- Laboratory tests (HbA1c, FPG, Total Cholesterol, LDL-C, HDL-C, Triglyceride, ALT, AST, Creatinine, e GFR, UACR, UGCR, etc.)
- Administration Information of Envlo Tab. or Envlomet SR Tab.
- AEs

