### Safety Analysis Set

Subjects who meet the inclusion/exclusion criteria, have been enrolled in this study, received the investigational product at least once according to the approved indications, and have undergone safety evaluations will be included in the safety analysis set.

1. **Methods of Analysis**
2. **General Principles**

Continuous variables will be presented as descriptive statistics (number of subjects, mean, standard deviation, median, minimum, maximum), and categorical variables will be presented as frequencies and percentages. Unless otherwise specified, all tests will be two-sided with a significance level of 5%. All p-values will be reported to a maximum of four decimal places. If not exactly divisible, values will be rounded to two decimal places, rounding up at the third decimal place.

1. **Demographic and Baseline Characteristics**

For the demographic data (age, gender, etc.) and baseline characteristics of the study subjects, continuous variables will be presented as mean, standard deviation, median, minimum, and maximum values, while categorical variables will be presented as frequency and percentage.

1. **Efficacy Endpoints**

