### Laboratory Tests

Descriptive statistics for laboratory tests will be presented at baseline, 12 weeks, and 24 weeks. Changes from baseline at 24 weeks will be analyzed using the Paired t-test or Wilcoxon signed rank test.

Additionally, the frequency and percentage of normal (Normal or NCS) and clinically significant abnormal (CS) changes will be summarized. Detailed information on subjects with clinically significant abnormal (CS) items will also be listed.

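### Laboratory changes are tested only in subjects whom routine care happens to retest; if retesting depends on the baseline value, regression to the mean can bias the change and push the false-positive rate above 5%

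*Protocol*

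**What the plan says.** Lipids, liver markers and renal markers are exploratory endpoints at 12 and 24 weeks (Protocol 8.1). Section 8.2, Exploratory Endpoints, states: "The change from baseline to 12 weeks or 24 weeks will be analyzed using a Paired t-test or Wilcoxon signed rank test". Secondary Efficacy Endpoints uses the same sentence, and so covers HbA1c and FPG. For safety, Section 8.2, Laboratory Tests, states: "Changes from baseline at 24 weeks will be analyzed using the Paired t-test or Wilcoxon signed rank test". The general principles in 8.2 set the error rate: "Unless otherwise specified, all tests will be two-sided with a significance level of 5" percent.

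Whether a laboratory value exists is left to the clinic. Note 8 to the data collection schedule reads: "Laboratory tests are collected if conducted as part of routine clinical practice". Section 4.3 reads: "There are no mandatory visits, tests, laboratory tests, or treatments in this study". Section 4.4 repeats the routine-care rule. The efficacy analysis set requires a post-baseline weight but sets no condition on laboratory values.

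**The concern.** A paired t-test or signed rank test drops every subject without a follow-up value. Here a subject can stay to week 24, have weight recorded, belong to the efficacy set and still contribute nothing to the ALT, UACR or lipid test. This is therefore separate from drop-out.

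A physician may have more reason to repeat an abnormal result than a normal one. If so, the pairs over-represent extreme baselines, and their follow-up values drift back towards the average without any drug effect.

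The direction depends on the marker. Where high values are repeated, the result is a false fall, which reads as improvement for total cholesterol, LDL-C, triglycerides, AST, ALT, gamma-GTP and UACR. For eGFR and HDL-C, low values would more plausibly be repeated, and the bias is then upward. In the safety tables the same shift could offset a true change in the other direction. At stake are the exploratory laboratory results, the laboratory safety changes, and HbA1c and FPG.

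**Working it through.** **The plan's own figure.** The protocol has no calculation for laboratory endpoints. Its only one is for weight: "Effect size: 0.25 (Mean of difference 2.5, SD of difference 10.0", power 0.95, two-sided 5%. An exact paired t-test gives n = 210 (power 0.9501), which agrees with "the total required sample size is estimated to be approximately 210 subjects". It then says: "Considering a drop-out rate of about 15%, we plan to recruit around 240 subjects". I take 240 × 0.85 = 204 subjects as available. The assumption list in the same section gives 30% drop-out, which conflicts with 15%; that is a separate matter.

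**Assumptions not in the protocol.** Correlation ρ between baseline and follow-up of 0.6 to 0.8; retest probabilities pL/pM/pH for the low, middle and high thirds of baseline; normal data with equal means and SDs at both times (no true change).

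**Formulas, in baseline SD units.**
- Mean of the top third of a normal distribution: 3 × φ(0.4307) = 3 × 0.3636 = 1.091. The bottom third is −1.091 and the middle third 0.
- Baseline mean of the retested: b = 1.091 × (pH − pL)/(pL + pM + pH).
- False mean change: s = −(1 − ρ) × b.
- Pairs: n = 204 × (pL + pM + pH)/3.
- SE ≈ √(2(1 − ρ)/n).
- Rejection ≈ Φ(|s|/SE − 1.96) + Φ(−|s|/SE − 1.96).

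**Example, 30/50/90% and ρ = 0.6.** b = 1.091 × 0.60/1.70 = 0.385. s = −0.4 × 0.385 = −0.154. n = 204 × 1.70/3 = 115.6. SE = √(0.8/115.6) = 0.083. The ratio is 1.85, and Φ(−0.11) = 0.46.

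| Retest % (low/mid/high) | Pairs | s at ρ 0.6 | s at ρ 0.8 | Reject, ρ 0.6 | Reject, ρ 0.8 |
|---|---|---|---|---|---|
| 50/50/50 | 102 | 0 | 0 | 5% | 5% |
| 80/85/95 | 177 | −0.025 | −0.013 | 7% | 6% |
| 40/50/70 | 109 | −0.082 | −0.041 | 16% | 10% |
| 30/50/90 | 116 | −0.154 | −0.077 | 46% | 26% |

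Simulations of 4,000 trials per case agree with these to within about two percentage points.

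**Second selection scheme.** Split at the baseline median, with 80% retested above and 40% below, and ρ = 0.7. The shift is −(0.3) × (0.4/1.2) × √(2/π) = −0.3 × 0.333 × 0.798 = −0.080 SD. Simulation gives −0.080 SD and rejection in about 20%, with the Wilcoxon test also at 20%. With 60/60% retesting the rate is about 5%.

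**Does the remedy work?** A likelihood estimate that regresses follow-up on baseline in the retested and evaluates it at the mean baseline of all 204 subjects rejects in about 5 to 6% across the normal-data cases by thirds, with bias no more than 0.003 SD. In the median-split case it rejects in 4.5%.

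**Skewed markers.** With lognormal data (log-SD 1.0, assumed) on the raw scale and ρ 0.6 to 0.8, the paired t-test rejects in about 6 to 8% at 40/50/70% and 10 to 16% at 30/50/90%. The raw-scale likelihood estimate is then itself biased upward by about 0.015 to 0.043 SD and rejects in only 1 to 2%. Logging such data returns the normal case above, so the model needs the log scale for these markers.

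**The case against.** **Selective retesting is nowhere documented.** This stands. The schedule marks laboratory tests at all three visits, and Section 4.3 lists a standard panel among the items for follow-up visits. If most clinics run that panel on nearly everyone, the inflation almost disappears, as the 80/85/95% row shows. A reader might infer that the paired tests will produce a significant improvement, or that the 5% level is already lost. The documents support neither: the level holds if retesting is unrelated to baseline, and even under the selective patterns tabulated the test rejects in fewer than half of trials.

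**Missing-data handling belongs in an SAP.** This does not answer the point. The protocol names the test, and that stated choice is what restricts the analysis to complete pairs. An SAP could still add a supportive model.

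**The safeguards and stakes are modest.** This stands in part. Summaries must report the number of subjects, and laboratory safety also has tables of normal and clinically significant changes with individual listings, so a harm need not go unseen. But counts alone do not show whether the retested differ at baseline. Most of the affected endpoints are exploratory, though HbA1c and FPG are secondary.

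**The normal-data figures overstate the effect for skewed markers.** This stands for raw-scale analysis, as shown in the working.

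**Conclusion.** The point holds as a conditional risk. The protocol leaves retesting to routine care and fixes a test that conditions on it; nothing in the protocol ensures that retesting is unrelated to the values. With no true change, rejection ranges from about 5% (unselective) through 6 to 7% (high coverage) and 10 to 16% (moderate selection) to 26 to 46% (strong selection), with false shifts up to about 0.15 SD. These figures rest on 204 subjects, normal data and assumed correlations and retest rates. They are smaller for right-skewed markers on the raw scale and for higher correlations. It would be wrong to read every affected marker as falling, since for eGFR and HDL-C the likely bias is upward. The point does not concern the primary weight and BMI analysis. A change should be made because it is cheap, not because an error has been shown.

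**What to change.** In Section 8.2, for laboratory changes under Exploratory Endpoints and Laboratory Tests, and for HbA1c and FPG under Secondary Efficacy Endpoints:

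- Estimate the mean change with a repeated-measures likelihood model: baseline, week 12 and week 24 as outcomes, visit as a factor, unstructured covariance, fitted to every subject with a baseline value, retested or not.
- Use the log scale for right-skewed markers (for example AST, ALT, gamma-GTP, triglycerides, UACR) and report a geometric mean ratio with 95% CI. Report other markers as a mean change with 95% CI.
- Keep the paired t-test or Wilcoxon test as supportive.
- Beside each result, show the baseline values of retested and not-retested subjects.

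The cost is revised wording and a little programming, with no new visits, tests or data. The model assumes that retesting depends on recorded values. It cannot correct for tests ordered on unrecorded grounds, or for missing baseline values, which are also optional here. If retesting proves unselective, the two analyses should agree closely.

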| **Design and Method of Observational Study** | This observational study is designed as a prospective, multicenter observational study to confirm the weight loss efficacy and safety of Envlo Tab. or Envlomet SR Tab. over 24 weeks in patients with Type 2 Diabetes in real-world primary care settings.  The study plans to recruit patients with Type 2 Diabetes who are scheduled to receive Envlo Tab. or Envlomet SR Tab. based on the medical judgment of the investigator (attending physician) and in accordance with the approved indications (effectiveness ∙ effect, administration∙ and dosage, precautions for use, etc.) in real-world clinical settings.  Regardless of whether they are currently undergoing pharmacotherapy for diabetes, all eligible patients who are considered suitable for Envlo Tab./Envlomet SR Tab. can be enrolled in this study. However, despite the decision to administer Envlo Tab./Envlomet SR Tab., observation is only possible with the subject's voluntary consent to participate in the study as determined by the investigator's medical judgment.  This observational study will collect demographic information, physical measurement, vital signs, and other relevant information up to 24 weeks after the administration of Envlo Tab./Envlomet SR Tab. in real-world clinical settings, irrespective of whether the medication is administered or not. Data will be collected based on medical records documented in real-world clinical settings. There are no mandatory visits, tests, or treatments specifically required by this observational study.  However, follow-up data collection will be conducted prospectively at approximately 12 weeks (±2 weeks) and 24 weeks (±2 weeks) from the date of subject registration (Visit 1, Baseline, Day 0). The data to be collected includes basic clinical information such as age, gender, past medical history and current medical history (hypertension, dyslipidemia, diabetes, cardiovascular and cerebrovascular diseases, cancer, etc.), lifestyle habits (smoking, alcohol consumption, physical activity), previous and concomitant medications (diabetes, hypertension, dyslipidemia treatments, etc.), as well as clinical indicators like weight, body composition analysis (BMI, body fat mass, muscle mass, etc.) using a body composition analyzer, fasting blood glucose, glycated hemoglobin (HbA1c), blood pressure (systolic/diastolic), total cholesterol, LDL cholesterol, HDL cholesterol, triglycerides, and safety evaluation parameters such as vital signs, laboratory tests, and adverse events. During the study, the investigator will collect the necessary data based on the information gathered during routine clinical care.  [figure not shown]  Visit 1  (0 day)  Visit 3  (24±2 weeks)  Visit 2  (12±2 weeks)  Baseline  Follow-Up Visits  Close-Out Visit (COV)  <Observational Study Flowchart> |

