Following these therapeutic guidelines, the use of SGLT-2 inhibitors has been increasing recently. SGLT-2 inhibitors increase urinary glucose excretion, leading to a relative decrease in insulin secretion and an increase in the glucagon/insulin ratio. This promotes lipolysis and increases ketone body production. The “Super-fuel” hypothesis suggests that in diabetic patients, ketone bodies in the blood serve as an effective energy source for the myocardium, improving cardiac function^8), 9)^. This metabolic benefit implies that SGLT-2 inhibitors can provide broad benefits beyond diabetes treatment, potentially aiding in managing obesity, hypertension, and dyslipidemia.

In particular, the glucose excreted in the urine due to SGLT-2 inhibitors is estimated to be 60-80 g daily, comparable to an energy expenditure of 230-310 kcal, similar to the energy burned by running for 30 minutes daily^10)^. Therefore, using SGLT-2 inhibitors in patients with diabetes who do not experience weight loss can still offer metabolic benefits related to weight reduction. The initial weight loss with SGLT-2 inhibitors is mainly due to reduced hepatic glycogen and dehydration. However, long-term weight loss involves increased fatty acid oxidation and a reduction in visceral and subcutaneous fat due to increased free fatty acid release from adipocytes^11)^. Existing literature indicates that the use of SGLT-2 inhibitors can result in a weight loss of approximately 2-3 kg within the first six months^11)^.

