## Secondary Objectives

The study will evaluate the following effects of administration of Envlo Tab. or Envlomet SR Tab.:

1. Change in BMI and weight at 12 weeks compared to baseline
2. Proportion of subjects achieving ≥5% reduction in BMI and weight at 12 and 24 weeks compared to baseline
3. Change in body composition index (body fat mass, visceral fat mass, muscle mass, waist/hip circumference) at 12 and 24 weeks compared to baseline
4. Change in HbA1c at 12 and 24 weeks compared to baseline
5. Change in FPG at 12 and 24 weeks compared to baseline
6. Change in blood pressure (systolic, diastolic) at 12 and 24 weeks compared to baseline
7. Proportion of subjects achieving HbA1c < 7% at 12 and 24 weeks compared to baseline
8. Proportion of subjects achieving HbA1c < 6.5% at 12 and 24 weeks compared to baseline
9. Proportion of subjects achieving therapeutic response [change in HbA1c (baseline HbA1c – HbA1c at each evaluation time point) > 0.5% or HbA1c < 7%] at 12 and 24 weeks compared to baseline

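### Blood-pressure and lipid changes are tested as raw single-arm before-after differences, and conflicting medication-recording rules may fail to capture the co-treatment changes needed to interpret them

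*Protocol*

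**What the plan says.** **Endpoints.** Protocol Section 2.2 lists "Change in blood pressure (systolic, diastolic) at 12 and 24 weeks compared to baseline" among the secondary objectives, and the synopsis agrees. The endpoint list in Section 8.1 leaves blood pressure out. Lipid changes are exploratory (Sections 2.3 and 8.1). Both objective sections introduce the changes as effects of giving the product, and Section 1.1 describes the class as "potentially aiding in managing obesity, hypertension, and dyslipidemia".

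**Test.** Under Exploratory Endpoints in Section 8.2: "The change from baseline to 12 weeks or 24 weeks will be analyzed using a Paired t-test or Wilcoxon signed rank test". The Secondary Efficacy Endpoints text is the same. Vital Signs and Laboratory Tests use the same paired tests at week 24. Under General Principles: "Unless otherwise specified, all tests will be two-sided with a significance level of 5" per cent. Section 8.2 gives co-medication no role; its Subgroup Analysis paragraph is optional and general.

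**Other treatment.** Section 9.9 leaves patients' care to clinical judgment, independent of the study. Antihypertensive and lipid-lowering drugs are neither restricted nor required to be stable.

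**Recording.** The synopsis plans to collect "previous and concomitant medications (diabetes, hypertension, dyslipidemia treatments, etc", and Section 4.1 says much the same. The notes to the data collection schedule say of prior medication: "Collect information on diabetes medications used specifically for the treatment of Type 2 Diabetes within 4 weeks prior to Visit 1". The same notes limit follow-up medication to drugs taken consistently for more than 3 months.

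**The concern.** With no comparator, any effect of a newly started or re-dosed statin or antihypertensive goes straight into the mean change, and the test cannot separate it from an enavogliflozin effect. New or stronger co-treatment would produce or exaggerate a fall; down-titration would hide one. Without a record of who changed treatment, the direction of the error is unknown.

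A supportive table by co-medication could be left to a statistical analysis plan. The data behind it could not. If the case report form follows the narrower recording rules, recent starts are lost at entry, and these are the patients whose values move most between baseline and week 24.

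**Working it through.** **1. Recording rules side by side (Protocol)**

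| Place | Prior drugs | At enrollment | Follow-up |
|---|---|---|---|
| Synopsis; Section 4.1 | diabetes, hypertension, dyslipidemia | – | same classes |
| Schedule notes | diabetes only, 4 weeks | – | all, if taken over 3 months |
| Section 4.3, Visit Schedule | diabetes only, 4 weeks | all drugs being taken | concomitant drugs, no limit stated |
| Section 4.4, Prior/Concomitant Medications | diabetes only, 4 weeks | those taken over 3 months | – |

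Three consequences follow.

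- *Before Visit 1.* A statin begun shortly before Visit 1 and still taken is recorded under Section 4.3, but not under Section 4.4.
- *Late in follow-up.* Three months is about 13 weeks, and 24 − 13 = 11. A drug started after about week 11 or 12 cannot have been taken for more than 3 months at week 24, so it can go unrecorded.
- *Older baseline samples.* The schedule notes and the Laboratory Tests item of Section 4.4 let a lipid result up to 3 months old stand as baseline. A statin started between that sample and Visit 1 acts inside the measured change, outside the prior-drug field and, under Section 4.4, outside the enrollment field too.

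**2. The plan's own figure.** Section 3.2 states "As a single-arm observational study, the number of subjects was calculated using G*Power 3.1.9.7", with "Effect size: 0.25 (Mean of difference 2.5, SD of difference 10.0"), power 0.95 and alpha 0.05. For a two-sided paired t-test, power is the probability that a noncentral t with n − 1 degrees of freedom and noncentrality 0.25√n lies beyond the critical value. At n = 210 this is 0.9501, so the stated 210 reproduces. It concerns weight; no effect or SD is given for blood pressure or lipids.

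Section 3.2 gives dropout as both 15% and 30%. Of 240 recruited, that leaves 240 × 0.85 = 204 or 240 × 0.70 = 168.

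**3. Effect of co-prescribing alone.** Assume no enavogliflozin effect. A fraction f starts a drug that lowers the value by D, and the SD of change is otherwise s.

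- Mean fall = f × D
- SD = √(s² + f(1 − f)D²)
- Noncentrality = (mean fall / SD) × √n, against a critical t of 1.972 at n = 204

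The values of f, D and s are assumptions; the protocol gives none. Example for LDL-C with f = 0.10, D = 35, s = 20: the mean fall is 3.5 mg/dL, SD = √(400 + 0.09 × 1225) = 22.59, and noncentrality = (3.5 / 22.59) × 14.28 = 2.21. The chance of a significant fall is 60%.

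| Measure | f | Mean fall | Significant fall, n = 204 | n = 168 |
|---|---|---|---|---|
| LDL-C (D = 35 mg/dL, s = 30 to 20) | 5% | 1.75 mg/dL | 12-21% | 11-18% |
| | 10% | 3.50 mg/dL | 35-60% | 29-51% |
| | 15% | 5.25 mg/dL | 63-89% | 55-82% |
| Systolic BP (D = 8 mmHg, s = 15 to 12) | 10% | 0.8 mmHg | 11-15% | 10-13% |
| | 20% | 1.6 mmHg | 32-45% | 27-38% |

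The nominal rate for a fall is 2.5%. A second LDL-C set (D = 40, s = 25-35, n = 204, either direction) gives 12-19%, 34-54% and 62-84% at 5%, 10% and 15%.

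**The case against.** **The analysis plan could supply the sensitivity analysis.** Section 8.2 names a basic test and does not rule out supportive analyses. This stands for the table, but not for the data: an analysis plan cannot use drug starts that the case report form never asked for.

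**Co-medication is collected.** This largely stands. Section 4.3 takes all drugs at enrollment, and Section 4.4 and the schedule notes ask for start and end dates and reasons for dose changes or discontinuation. A reader might infer that the protocol ignores these drugs altogether. The documents do not support that: collection is partial and contradictory, and dose changes in a long-standing drug would be captured.

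**The size rests on assumed inputs.** This stands. A reader might infer that the study will report a false improvement. Nothing in the documents gives prescribing rates, so only the possibility is shown. With 2% starting a statin (D = 35), the chance is 5-7% at n = 204. Laboratory values are collected only if done in routine care, so fewer than 204 may have paired lipids. That lowers the chance of significance but leaves the mean bias, f × D, unchanged.

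**Other before-after confounding remains.** This also stands. Planned diet and exercise (Section 3.3, criterion 4) and regression to the mean would act even in patients on unchanged co-treatment.

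**Conclusion.** The concern holds in a limited form. The protocol fixes unadjusted single-arm tests for blood pressure and lipids, presents the changes as effects of the product, and contradicts itself on which other drugs are recorded. The 3-month rule, and a lipid baseline that may predate Visit 1 by up to 3 months, open gaps where recent starts matter most.

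If 5-15% start a statin, under the assumptions above, a significant LDL-C fall with no drug effect appears in roughly 12-89% of studies (n = 204), against 2.5% nominal. For systolic pressure the bias is 0.8-1.6 mmHg if 10-20% intensify. The calculation models only starts and intensifications; reductions in co-treatment would act the other way.

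Priority is low to moderate: the endpoints are secondary and exploratory, and the concern does not touch the weight and BMI primary endpoint.

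**What to change.** 1. Reconcile the synopsis, the schedule notes and Sections 4.1, 4.3 and 4.4, so that antihypertensive and lipid-lowering drugs are recorded with start, stop and dose-change dates whatever their duration. The look-back should reach the date of the baseline measurement actually used; for lipids that may be up to 3 months before Visit 1. Widening only the 4-week prior-drug field would not be enough: with the 3-month rule left in place, late starters would be misclassified as unchanged.
2. In Section 8.2, report beside each blood-pressure and lipid result the number of patients whose relevant treatment changed, and a supportive analysis in those whose treatment was unchanged from the baseline measurement to the visit.

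**Cost.** A slightly longer medication page in the existing case report form and two supportive tables. The form change has to be made prospectively. The unchanged-treatment subset is smaller and selected after baseline, so it supports the main result without replacing it, and it does not make the change attributable to enavogliflozin.
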